All participants will receive usual care education (UCE), which includes transplant specific information for the recipient and the caregiver, as well as caregiver resources. After study enrollment, caregiver subjects will be randomized to either the control group or the intervention group. A permuted block randomization with allocation ratio of 1:1 will be performed by the study statistician. All participants will meet 1:1 with a study investigator to review the UCE materials. Participants in the intervention group will also receive an audio recording of a 20 minute yoga-based stress reduction intervention, as well as instructions on how to complete the intervention; they will be asked to practice the twenty minute audio file daily for the six weeks of the intervention. The six-week length of the intervention, as well as the 20 minute time of the audio file, was selected based upon the length of similar interventions in other caregiver populations, with interventions ranging between four to ten weeks [^37^](#_ENREF_37)^,^[^43^](#_ENREF_43). All study visits will be scheduled around the HSCT recipient’s schedule and visits to minimize burden for the caregiver. The initial visit for all participants will occur prior to the patient’s initial discharge from the hospital and within 7 days of the HSCT infusion (Day 0+7). Subjects in the intervention group will receive a brief phone call at weeks two and four (+/- 7 days) to assess progress and to record practice. All subjects will participate in an exit interview at week six (+/- 7 days). Study questionnaires will be administered to all subjects at baseline and again at week six (+/- 7 days). Completion will take approximately 20 minutes through a web-based system. If the electronic system is unavailable, a hard copy of the questionnaires will be available for completion. Caregivers in either group who complete baseline assessments but are no longer able to return to the clinical center for their week 6 study visit will be given the option to complete the week 6 questionnaires electronically.

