## 3.2 Experimental Intervention – Stress reduction intervention Appendix A

After baseline measures have been obtained and subjects have been randomized into the intervention and control groups, subjects in the intervention group will meet with the interventionist for approximately 20 minutes to go over instructions for performing the gentle chair yoga and breath work that they will be asked to perform daily using a 20-minute audio recording that they will receive in this meeting. The stress reduction intervention (Appendix A) will be provided to subjects by a trained interventionist. The intervention will be delivered by [name], RN, who is a registered nurse with a master’s degree in psychiatric-mental health nursing, and is a certified Iyengar Yoga Instructor, or by study staff who have received training by [name]. Participants will then practice the recording one time under the supervision of study staff.

The audio recording was developed by Advanced Iyengar Yoga Instructor, [name], who has over 35 years of experience teaching yoga and has recorded numerous audiotapes of yoga for home practice. [name] worked with [name] to develop the intervention, based upon [name] years of teaching experience, as well as the research literature that shows the effectiveness of similar yogic breathing exercises in reducing levels of perceived stress [^53^](#_ENREF_53) and similar chair-based yoga interventions in improving levels of depression, anxiety, quality of life, and well-being in elderly populations [^54^](#_ENREF_54)^,^[^55^](#_ENREF_55). The 20-minute audio recording will lead participants through a series of gentle stretching and breathing exercises [^53-55^](#_ENREF_53). The first few poses will be performed standing, using the wall for support. The remainder of the audio file will consist of gentle seated yoga poses (stretches and twists) that are performed in a chair, as well as guided breathing exercises that focus primarily on slowing and quieting the inhalations and exhalations.

Small (<5 GB) audio players will be purchased and given to subjects in the intervention group. These devices will be preloaded with the 20-minute audio file of the stress reduction intervention. Upon completion of the study, control group subjects will also receive an audio player with the intervention recording and no subjects will be asked to return their device.

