## 6.2 Statistical Analyses

Initial data analysis will consist of examining the frequency distributions for all variables at both time points and computing descriptive statistics appropriate for the level of measurement (e.g., mean and standard deviation for interval level data, median for ordinal level data). Linear mixed repeated measures analysis will be used to analyze the effect of intervention on the primary outcome of perceived stress. The primary analysis will be based on intention-to-treat, which will include all of the randomized subjects. The last observation carried forward method will be used to impute missing data. However, if an enrolled subject comes off study before being randomized, they will be replaced. A sensitivity analysis will be performed for all subjects with complete data at both time points.

The effect of intervention on the exploratory outcome variables as described in the objective section will also be examined by linear mixed models. Any demographic covariates will be included in the model if significantly associated with the outcome and significantly different between the groups. To examine the effect of practice variation on the study outcomes, practice time will be included in the linear mixed models for the intervention group only. Aikake information criterion and the Bayesian information criterion will be used to select best fitting models. Appropriate data transformation technique will be used if necessary.

If no significant differences are found between groups, the responders with clinically meaningful changes in the intervention group will then be characterized. No minimal clinically important differences have been established for our primary outcome, the PSS, therefore, we will use the method proposed by Norman, Sloan, and Wyrwich (2003) of accepting changes in .5 standard deviation as clinically important [^87^](#_ENREF_87). Responders and non-responders will be compared on the basis of their demographic characteristics such as gender and age.

In addition to the primary analysis outlined above, exploratory hypotheses generating analyses will be performed to examine the relationships among caregiver factors. Methods of correlation and regression analysis will be used to evaluate the relationships between outcomes of interest and study variables. All inferential tests will be conducted at the .05 level of significance.

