# 8.0 Collecting, Tracking and Disposition of Data & Samples

## 8.1 Samples Management

During the course of participating in this study survey, clinical data, and biological specimens (i.e. blood) will be collected as described in Figures 2 and 3. These data will be used as outlined in the study objectives. Data from all subjects removed from the study will be included in the intention-to-treat analysis.

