# 10.0 HUMAN SUBJECT PROTECTIONS

## 10.1 Rationale for Subject Selection

The following populations will be excluded from participation in this study and are in accordance with the following NIH HRPP SOPs: 14A Research Involving Vulnerable Subjects, 14B Research Involving Pregnant Women, Human Fetuses and Neonates, 14D Research Involving Children, and 14E Research Involving Adults who are or may be Unable to Consent. Subjects who do not speak and read English will be excluded because the intervention requires the use of an audio-file that is not available in other languages at this time. Pregnant and lactating women are excluded from participation due to the inherent physiological changes that are associated with these circumstances. Children and those unable to provide informed consent or do not understand the investigational nature of the study are excluded because the intervention requires a level of self-responsibility that is likely a problem with these populations.

In our previous study of transplant caregivers, there was a 10% attrition rate for caregivers related to patient death and other complicating factors. Patients receiving an allogeneic transplantation are quite ill and may die during the study period at which point the caregiver(s) would be removed from study. Because the death of a loved one may result in additional stress and the intervention may be helpful in reducing stress, subjects in the intervention group who are removed from the study will be encouraged to keep the audio file and continue practicing the exercises if they find them beneficial. Individuals in the control group who are removed from the study will be given the option of receiving the CD and instructions for the audio file, should they desire to do so. Because the burden of the study may be a deterrent for caregiver participation, we are including compensation for their participation and inconvenience for this study.

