## 10.3 Consent and Assent Processes and Documents

The principal investigator or designated associate investigators (section 10.3.1) will obtain informed consent. If the subject is not able to articulate understanding of the study, they will not be enrolled. An assent process is not required since children under the age of 18 will not be included. If the participant is known or reports that they are an NIH employee and is interested in participating in this study, they will be referred to the NIH Manual Chapter 2300-630-3, which details the NIH Leave Policy for NIH employees who wish to participate in an NIH biomedical research studies. Additionally, NIH HRPP SOP 14F, Research Involving NIH Staff as Subjects, will be reviewed and Appendix B: NIH Information Sheet on Staff Research Participation will be given to the subject prior to signing the consent document and participating in the study.

**10.3.1** Consent Process, Associate Investigators

The consent will be obtained by the principal investigator or any of the following associate investigators: [name], MS, RN, CRNP-BC, OCN^®^, [name], BSN, OCN^®,^ [name], PhD; [name], CRNP, MS, AOCN^®^; [name], BSN, OCN^®^ and are indicated by a “*” on the protocol investigator list.

Consenting Investigators will provide each potential participant:

- A brief explanation of the study emphasizing the amount of time involved completing study questionnaires and study visits are incorporated.
- Review biological samples intended for collection and schedule.
- Provision of written consent form time for independent review.
- Verbal consenting process beginning with ‘test’ questions to assess comprehension of important study points outlined in the written consent form.

Potential subjects will be encouraged to ask questions prior to enrolling in this study. The subjects will be reassured that participation in this study is entirely voluntary. Subjects will be informed that their decision to participate or decline in this study will have no impact on their participation in other clinical protocols at the NIH or the transplant recipients’ care. Additionally, once enrolled, the subject has the right to withdraw from this study at any time. Furthermore, if the subject’s HSCT recipient expires during the study period, the caregiver subject will be removed from study on the HSCT recipient’s date of death.

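### With only two assessments, last observation carried forward enters every caregiver without a week-6 stress score as exactly zero change in the primary analysis

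*Protocol*

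**What the plan says.** Protocol section 6.2 names the primary method: "Linear mixed repeated measures analysis will be used to analyze the effect of intervention on the primary outcome of perceived stress". It defines the analysis set: "The primary analysis will be based on intention-to-treat, which will include all of the randomized subjects". It then fixes how gaps are filled: "The last observation carried forward method will be used to impute missing data". The only sensitivity analysis it names uses subjects with complete data at both time points.

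The measurement schedule is in section 3.0: "Study questionnaires will be administered to all subjects at baseline and again at week six (+/- 7 days". Figure 3 agrees and shows perceived stress at those two points only. The contacts at weeks 2 and 4 are telephone calls to the intervention group about practice (Figure 3, Appendix D) and yield no stress score. Section 3.2 places baseline assessment ahead of the intervention session ("After baseline measures have been obtained and subjects have been randomized into the intervention and control groups"), so a randomised caregiver should have a baseline value.

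On bereavement, section 10.3 says that "the caregiver subject will be removed from study on the HSCT recipient’s date of death", and section 8.1 that "Data from all subjects removed from the study will be included in the intention-to-treat analysis". Section 10.1 reports that in the group's earlier caregiver study "there was a 10% attrition rate for caregivers related to patient death and other complicating factors", and acknowledges that losing the patient may add to a caregiver's stress. Section 3.0 lets caregivers who cannot return at week 6 answer the questionnaires electronically.

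**The concern.** When an outcome has one baseline and one follow-up value, carrying the last observation forward is the same as carrying baseline forward. The rule then asserts that each caregiver without a week-6 score has exactly the stress recorded around the infusion. For bereaved caregivers this conflicts with what the protocol itself expects.

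The imputation is also unnecessary. A linear mixed model fitted by likelihood already uses caregivers who have only a baseline value, under a missing-at-random assumption. Imputing first replaces that assumption with a fixed zero change and treats the filled-in values as if they had been observed.

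What is at stake is the primary estimate. With equal loss it can be diluted. With unequal loss and a general drift in stress, it can be biased in either direction.

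**Working it through.** **Inputs from the protocol.** Section 6.1: effect size 0.6 SD, correlation 0.80 between time points, two-sided alpha 0.05, 80% power, 39 per group. Section 10.1: 10% attrition. **Assumed:** loss rates by arm and any common change in stress; the protocol gives neither.

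**The plan's own figure.** n = 2(z₀.₉₇₅ + z₀.₈₀)²/d² = 43.60 per group for a week-6-only comparison with d = 0.6. Multiplied by (1 + 0.80)/2 = 0.9, the factor for the average of two exchangeable time points, this gives 39.24, which matches the stated 39. The match confirms the inputs used below. No allowance for attrition is included. At 10%, about 0.10 × 39 = 3.9 caregivers per arm, or 7.8 of 78, would have an imputed value.

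**Expected estimate after carrying baseline forward.** Let s be the mean change in controls, s − δ the mean change in the intervention arm, and p_C, p_T the fractions missing. Each imputed change is 0. If loss is random within arm, the expected difference in change (control minus intervention) is

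(1 − p_C)·s − (1 − p_T)·(s − δ).

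- Equal loss p: this reduces to (1 − p)·δ. At p = 0.10, 0.90 × 0.60 = 0.54 SD. At p = 0.20, 0.80 × 0.60 = 0.48 SD.
- No effect (δ = 0), unequal loss: this reduces to (p_T − p_C)·s. For 15% v 5% loss, 0.10 × 0.5 = 0.05 SD with a common change of 0.5 SD, and 0.10 × 1.0 = 0.10 SD with a common change of 1 SD. The sign reverses if the arms are swapped.

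**Error rates.** These come from simulated trials with 39 per arm, correlation 0.80, a t-test on change, values deleted at random within arm, and 4,000 trials per scenario. The simulation standard error at 5% is √(0.05 × 0.95/4000) ≈ 0.3 percentage points. With the data filled in at both time points, the t-test on change is the group-by-time contrast of a two-occasion mixed model.

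| True effect | Common change | Loss (intervention v control) | Mean estimate, carried forward | Rejection rate, carried forward | Rejection rate, complete cases |
|---|---|---|---|---|---|
| 0.60 SD | 0 | 10% v 10% | 0.54 | 97.5% | 97.8% |
| 0.60 SD | 0 | 20% v 20% | 0.48 | 94.4% | 94.9% |
| 0 | 0.5 SD | 10% v 10% | 0.00 | 5.4% | 5.4% |
| 0 | 0.5 SD | 5% v 15% | −0.05 | 7.0% | 5.1% |
| 0 | 1 SD | 5% v 15% | −0.10 | 10.2% | 4.8% |
| 0 | 1 SD | 15% v 5% | +0.10 | 10.5% | 5.3% |

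With 5% v 15% loss and no common change, the carried-forward type I error was 4.7% in a further set of 8,000 trials. Unequal loss alone does not inflate it; a drift in both arms is needed as well.

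**The case against.** The strongest reply is that the documented harm is modest. The only attrition figure is 10%. With equal loss the cost is 0.06 SD of dilution, type I error is unaffected, and power on a change-score test is essentially the same with or without the rule. The Precis describes the study as one of preliminary effectiveness. All of this stands.

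A reader might go further and infer that the primary test has an inflated false-positive rate. The documents do not support that. Inflation needs unequal loss and a sizeable common change together, and the protocol states neither. Recipient deaths have no evident reason to differ by arm. Withdrawal could differ, since only one arm is asked to practise daily, but its size is unknown. A more extreme case (5% v 25% loss with a 1 SD change) takes type I error to about 25%, but nothing in the protocol points to such rates.

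A reader might also infer that the mixed model without imputation cures the bereavement problem. The simulations do not show this, because they delete values at random within arm. If bereavement raises unobserved stress, the mixed model can also be biased.

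Nor is the planned complete-case analysis worthless. Under random loss within arm its contrast correlates about 0.99 with the mixed-model contrast, with nearly the same standard deviation (0.151 v 0.150), so it would reveal distortion of the kind simulated. It cannot show how far the result depends on the unobserved stress of the caregivers it leaves out.

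Two further qualifications stand. The figure of 0.54 SD is a dilution only if those lost would have had the same effect as those observed. If they would have gained nothing, 0.90 × 0.60 + 0.10 × 0 = 0.54 SD is itself the effect in all randomised caregivers. The electronic option in section 3.0 should also reduce missing scores, although the protocol does not extend it to bereaved caregivers removed from study.

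**Conclusion.** The point holds as a defect in the stated primary analysis. Section 6.2 fixes the imputation rule in the protocol itself, so this is not detail left to a statistical analysis plan. With assessments only at baseline and week 6, the rule sets every missing change to zero, including for bereaved caregivers whom the protocol expects may be more stressed.

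At the protocol's 10% attrition, equal across arms and random within arm, the size is a dilution from 0.60 to 0.54 SD, with type I error of about 5% and change-score power of about 97%. A spurious difference of 0.05 to 0.10 SD, with type I error of about 7 to 10%, follows only under the assumed 5% v 15% loss and a common change of 0.5 to 1 SD. The case for change rests on an implausible and needless assumption that is cheap to remove, not on a demonstrated loss of error control.

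**What to change.** - Delete the imputation sentence from section 6.2.
- State that the linear mixed model is fitted by REML to all observed baseline and week-6 perceived-stress values of all randomised caregivers, without imputation. Everyone with a baseline value stays in the analysis, under missing at random, so the intention-to-treat commitments in sections 6.2 and 8.1 are still met.
- Apply the same rule to the exploratory outcomes.
- Keep the complete-case analysis.
- Add a delta-adjusted sensitivity analysis that shifts the unobserved week-6 values over a stated range, because missing at random is doubtful for bereaved caregivers. Its absence from the protocol is not a fault in itself; it is proposed because the mixed model cannot settle that question.

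The cost is a wording change and one extra analysis. No new data, visits or participants are needed. The change should be made before outcome data are examined.

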## Exclusion criteria

- - - Age < 18 years old
    - Pregnant or lactating women
    - Inability to comprehend investigational nature of study
    - Inability to provide informed consent
    - Unable to read and speak English
    - Does not agree to participate in study or follow study design
    - Serving as a paid caregiver for any individual
    - Regular practitioner of yoga, meditation or other mind-body practice (definition: taking classes or practicing at least weekly for at least 2 of the past 6 months).
    - Physical function limitations that would interfere with intervention

Caregiver participants will be excluded from the biomarker analysis if they have had:

- - - Glucocorticosteroid treatment in the last 2 months
    - Have a recent (within the last 2 months) acute illness or injury
    - Have served as a stem cell transplant donor or have taken filgastrim

*****If more than one caregiver is planned for the transplant recipient during the transplant phase, only 1 caregiver will be eligible to participate in the study. An active caregiver is defined as someone who lives with or provides care regularly for the HSCT recipient during the 6 week study period. Caregivers will be categorized as to whether they are the sole caregiver versus one of multiple caregivers.

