# 6.0 BIOSTATISTICAL CONSIDERATIONS

## 6.1 Sample size

The study is a randomized controlled trial with two groups: stress reduction and control (standard education) using permuted block randomization with allocation ratio of 1:1. The primary objective of this study is to investigate whether HSCT caregivers in the stress reduction group demonstrate improved levels of stress compared to those in the control group. Power analysis was performed based on the primary objective only. We used a two-sided hypothesis that the PSS level will differ between the intervention group and the control group. We assume an exchangeable correlation structure of PSS. Based on an effect size of 0.6 [^40^](#_ENREF_40)^,^[^85^](#_ENREF_85) and correlation of 0.80 between two time points from our biomarker study, with 80% power and type I error of 0.05, in order to detect a difference between the stress reduction group and the control group, we will need 39 participants in each group and a total sample size of 78 [^86^](#_ENREF_86).

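### Demographic covariates enter a model only if they are significantly imbalanced and significantly prognostic, a rule that forgoes precision and fixes the model after the data are seen

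*Protocol*

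**What the plan says.** Section 6.2 gives the primary outcome its own paragraph: "Linear mixed repeated measures analysis will be used to analyze the effect of intervention on the primary outcome of perceived stress". No covariates are named there.

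The next paragraph opens with the exploratory outcomes: "The effect of intervention on the exploratory outcome variables as described in the objective section will also be examined by linear mixed models". The covariate rule follows at once: "Any demographic covariates will be included in the model if significantly associated with the outcome and significantly different between the groups". After a sentence on practice time in the intervention arm comes: "Aikake information criterion and the Bayesian information criterion will be used to select best fitting models". No covariate list or candidate set of models is given.

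The section closes with the level that applies to the entry tests as well: "All inferential tests will be conducted at the .05 level of significance".

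Suitable covariates are already collected. Section 6.2 mentions gender and age, and section 4.2 says: "Caregivers will be categorized as to whether they are the sole caregiver versus one of multiple caregivers". Section 5.2 records the same item in the demographic interview.

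**The concern.** Sections 3.0 and 6.1 specify 1:1 permuted-block allocation. If allocation is sound, any baseline difference between arms is due to chance, and testing it for significance says nothing about whether adjustment would help. What matters for precision is how strongly the covariate predicts the outcome. By requiring significant imbalance as well, the rule discards a strongly prognostic covariate roughly 19 times in 20.

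The rule also cannot be applied until covariates have been tested against both the outcome and the arm. The covariate set, the estimate and its standard error therefore depend on the data. A later analysis plan that follows the protocol inherits this. It is a rule fixed badly, rather than a detail left open.

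The trial plans 78 caregivers, so precision that could be had for nothing is worth keeping.

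**Working it through.** **Inputs from section 6.1.** 39 per arm; two-sided 0.05 ("We used a two-sided hypothesis that the PSS level will differ between the intervention group and the control group"); "Based on an effect size of 0.6" (in SD units); correlation 0.80 between visits, exchangeable; power 80%. **Assumed, because the protocol gives none:** the correlation r of a demographic covariate with the outcome (0.3 to 0.5, equal at both visits), or the share R² of outcome variance that demographics explain (10% or 30%).

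**Step 1: the plan's own figure.** n per arm = 2(1.960 + 0.842)²/0.6² = 43.60. Multiplying by the time-averaged factor (1 + 0.80)/2 = 0.90 gives 39.24, against the stated 39. Power at 39 is 79.8%. The figure reproduces and does not depend on the covariate rule.

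**Step 2: how often the rule admits a covariate.** The imbalance test alone passes 5% of the time. Both conditions together passed in 3% to 4% of 6,000 simulated trials at r = 0.3 and about 5% at r = 0.5. With several covariates some imbalance is common: 1 − 0.95⁶ = 26% for at least one of six independent covariates. Even so, with six covariates the rule admitted any of them in only 3–7% of trials with baseline adjusted, and 6–14% without.

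**Step 3: what is forgone, one covariate.** SE = √(2v/39) and power = Φ(δ/SE − 1.96), where v is the residual variance with the covariate in the model (r = 0 means left out):

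- week 6 only: v = 1 − r²
- time-averaged: v = 0.90 − r²
- change from baseline: v = 2(1 − 0.80) = 0.40 for any r, because the covariate cancels
- baseline-adjusted: v = (1 − r²) − (0.80 − r²)²/(1 − r²)

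For the last two, 0.6 SD gives about 99% power whatever is done, so δ = 0.4 SD is used to make a loss visible.

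| Contrast | δ | v: r = 0 / 0.3 / 0.5 | Power: r = 0 / 0.3 / 0.5 |
|---|---|---|---|
| Week 6 only | 0.6 | 1 / 0.91 / 0.75 | 75.5 / 79.3 / 86.4% |
| Time-averaged | 0.6 | 0.90 / 0.81 / 0.65 | 79.8 / 83.7 / 90.8% |
| Change | 0.4 | 0.40 / 0.40 / 0.40 | 79.8 / 79.8 / 79.8% |
| Baseline-adjusted | 0.4 | 0.360 / 0.356 / 0.347 | 83.7 / 84.1 / 85.1% |

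This normal approximation compares never with always including the covariate and ignores degrees of freedom. Simulations (6,000 trials per setting) compared the rule itself with always including:

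- week 6 only: 74.8 v 78.3% (r = 0.3), 74.9 v 84.8% (r = 0.5)
- time-averaged: 79.0 v 82.0%, 79.9 v 89.6%
- baseline-adjusted: 81.7 v 82.0% (r = 0.3). At r = 0.5, a run of 4,000 trials comparing the model without and with the covariate gave 81.9 v 82.2%, with SE 0.137 v 0.135.

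**Step 4: six covariates that predict beyond baseline** (6,000 trials per setting, baseline adjusted, δ = 0.4 SD). Power under the rule v all six prespecified: 81.8 v 82.9% at R² = 0.10, and 82.5 v 91.4% at R² = 0.30, where R² is the share of variance remaining after baseline. Without baseline and at 0.6 SD: 74.8 v 75.6% and 73.7 v 84.7%, R² then being the share of outcome variance.

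**Step 5: type I error.** Under the rule it was 4.5–4.9% with six covariates and 4.2–5.1% with one at r = 0.3 to 0.5; in the week-6-only model it fell to 2.8% at an assumed r of 0.8. Prespecified adjustment with six covariates gave 4.7–5.2%. If AIC were used to choose covariates, it rose to 5.6–6.4%.

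**The case against.** The strongest reply has four parts.

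- **Scope.** Both sentences sit in the exploratory-outcome paragraph, and section 6.1 powers the primary objective only. A reader might infer that the primary test is at risk. The text does not establish that: it neither extends the rule to the primary model nor excludes it. This stands, and the point is limited accordingly.
- **Size.** The planned model uses two visits with an assumed correlation of 0.80. Once baseline carries that information, a demographic variable acting equally at both visits adds almost nothing. As a main effect it leaves a group-by-time contrast unchanged when data are complete, and carrying the last observation forward largely makes them so. This stands. A standard error 14% too large, or a 10-point power loss, belongs to a week-6-only model at a correlation of 0.5 (a time-averaged contrast loses about as much power) and is not a general result. No figure in the protocol supports correlations that high, or an R² of 30%, for demographics.
- **False positives.** A reader might expect data-driven covariate entry to inflate type I error. This rule does not; it is neutral to conservative.
- **AIC/BIC.** That sentence follows the practice-time models in the intervention arm and may refer to those or to covariance structure. The protocol does not say that it selects the between-group model, so the 5.6–6.4% is conditional on that reading. Nor is it right that two visits leave nothing to select: compound symmetry (two parameters) and unstructured (three) are real alternatives.

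The reply does not rescue the rule itself. Testing imbalance after randomisation is not a sound basis for adjustment under any of these readings.

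**Conclusion.** The concern holds in limited form. Section 6.2 fixes a covariate entry rule that turns on chance imbalance, leaves prognostic demographics out about 95% of the time, and settles the model only after outcome and arm have been examined. It certainly covers the exploratory treatment-effect models; its reach to the primary model is unstated, and that ambiguity should itself be resolved.

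The harm is lost precision, with no excess of false positives. It ranges from practically nothing (baseline adjusted or change tested, covariate acting equally at both visits) to about 4 to 10 power points (time-averaged or week-6-only, r of 0.3 to 0.5). Demographics explaining 30% of the variance left after baseline would make it about 9 points in a baseline-adjusted model. Every non-trivial figure rests on an assumed covariate strength. The stated sample size is unaffected.

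**What to change.** In section 6.2:

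1. Delete the significance-based entry rule.
2. Adjust each treatment-effect model for the baseline value of its own outcome plus a short list of covariates named before outcomes are examined by arm, whatever any imbalance test shows. Age, sex and sole versus multiple caregiver are examples already collected.
3. State that the same approach applies to the primary analysis of perceived stress.
4. Limit AIC/BIC to covariance structure, or to the intervention-arm practice-time models and the hypothesis-generating regressions, and say that they do not choose the covariates of a between-group model.

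The cost is a change of wording and a few degrees of freedom per model. No new data are needed and the sample size does not change. If the covariates turn out weak, almost nothing is lost: in the baseline-adjusted simulation at r = 0.3, power was 82.0% with the covariate always in and 81.7% under the rule.
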